### Data collection and management

2.8

Both quantitative and qualitative data will be collected from all included participants. Feedback from the children and their family caregivers will be collected via the exer-app, via a questionnaire on usability, and through semi-structured interviews (23).

Qualitative data will be collected through questionnaire and semi-structured interviews performed after each exercise period, including the effectiveness testing before and after. The semi-structured interviews will take place at the children's home or through Teams online. The child will be asked to be interviewed first, followed by the caregiver within the same session. The total duration of each session is estimated to be approximately one hour. The supervising personal trainer will be instructed to take fieldnotes after each exercise session and will be semi-structurally interviewed in person (23) after each exercise period. All semi-structured interviews will be audio recorded and field notes documented after by interviewer.

The semi-structured interviews will be performed by a doctoral student under supervision from the research team (TJ: doctoral student, physiotherapist; KL: supervisor, physiotherapist specialized in paediatrics; [name]: engineer with PhD in computer science; ÅA: professor of biomedical science; OH: geneticist; RH: supervisor, organizational psychologist; [name]: main supervisor, physiotherapist specialized in exercise and physical activity). The research team consists of four females and four men in total. Transcripts will not be returned to participants for comments.

Quantitative data will be collected in the exer-app after each exercise session. The children will be asked to fill in information about the perceived exertion of the exercise session, according to the Borg scale (45), and pain, according to the Faces Pain Scale-Revised (46). The number of exercise sessions will be registered through the children marking the session as done in the app. During each exercise session, heart rate and workload will be continuously collected from the bike into the exer-app. Questions about adverse events will be sent out prior to each exercise testing (supplementary S7).

All data collected will be pseudoanonymised and securely stored at Lund University, with access restricted to the research team. Confidentiality will be maintained, and findings reported without traceable individual data.

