#### Feasibility analysis

2.9.1

To structure the feasibility analysis process, scientific, management, and resource (33) uncertainties will be assessed (Table 1). The analysis will have an intent-to-treat (ITT) approach where above 66% of successful cases will be considered feasible, adjustable if successful cases fall between 20% and 65%, and unfeasible if the successful case rate is below 20%, both for individual outcomes and for an overall analysis. Wide thresholds were chosen to allow for iterative refinement of the intervention based on participatory feedback during study. When items are considered adjustable, the data collected from the android tablet computer, field notes, and interviews will be used to further develop the HOME-EX protocol.

**Table 1 T1:** Description of predefined progression criteria.

Items	Outcomes	Predefined progression criteria
***Process:*** This assesses the feasibility of the processes that are key to the success of the main study. Evaluation of study design (e.g., reducing uncertainty around recruitment, data collection, retention, outcomes, and analysis)		
Recruitment	Recruitment rate	>66% of invited participants accepted to participate in the study
		65%–20% of invited participants agreed to participate in the study
		<19% of invited participants agreed to participate in the study
Retention	Retention rate	>66% completed all exercise periods
		65–20% completed all exercise periods
		<19% completed all exercise periods
Data collection	Completion rate and perceived usefulness	>66% completed all procedures and are perceived as useful/acceptable
		65%–20% completed all procedures and perceived them as useful/acceptable
		<19% completed all procedures and perceived them as useful/acceptable
Outcome measures	Variance and distribution of collected data	Outcomes provide interpretable data with acceptable variance
		Outcomes partially interpretable, large variance
		Outcomes are not interpretable, excessive variance
***Scientific:*** This deals with the assessment of treatment safety, dose, response, effect, and variance of the effect (study design)		
Outcome measures	Variance and distribution of collected data	Outcomes provide interpretable data with acceptable variance
		Outcomes partially interpretable, large variance
		Outcomes not interpretable, excessive variance
Acceptability	Perceived acceptability of the eHealth tablet app and home-based exercise	>66% report app/exercise acceptable

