		65%–20% report app/exercise acceptable
		<19% report app/exercise acceptable
Usability/technical demands	Technical support needed	Only initial introduction needed
		Required equal time for support as for tablet app use
		Unable to use eHealth app due to technical demands
Barriers/facilitators	Perceived barriers and facilitators when exercising and using eHealth tablet app	Perceived more facilitators than barriers
		Equal numbers of facilitators as barriers
		Perceived more barriers than facilitators
***Management:*** This covers potential human and data management problems		
Capacity to deliver exercise sessions	Trainers' capacity to deliver exercise intervention	>66% completed exercise sessions
		65%–20% completed exercise sessions
		<19% completed exercise sessions
Capacity to deliver exercise equipment	Logistics in delivering cycle ergometers to children's homes	>66% successful deliveries
		65%–20% successful deliveries
		<19% successful deliveries
***Recourses:*** This pertains to assessing time and resource problems that can occur during the main study		
Resources to deliver	Exercise intervention	Trainer reports delivery of exercise sessions as feasible with given resources
		Trainer reports delivery possible but challenging
		Provider reports delivery not feasible
Resources to deliver	Effectiveness testing	The coordination of all tests is feasible within resources
		The coordination of all tests is possible but challenging
		Provider reports delivery not feasible
Resources to deliver	Logistics to deliver cycle ergometers to children's homes	The coordination of all tests is feasible within resources
		The coordination of all tests is possible but challenging
		Provider reports delivery not feasible

Process uncertainties will include as recruitment rate, retention rate, acceptability, usability, barriers/facilitators, and adherence. Scientific uncertainties will include safety, dose, and variance of effect, all aspects related to the study design planned for a future efficacy study, Management uncertainties will address data collection processes, while resource-related uncertainties will assess the time and resource problems involved in running the study (33) (see Table 1 on progress criteria).

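### Safety is a named uncertainty with no progression criterion in Table 1, and no adverse-event form is stated after the final exercise test

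*Protocol article*

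**What the plan says.** Section 2.9.1 organises the feasibility analysis into process, scientific, management and resource uncertainties, and refers to Table 1 for the progression criteria. The Scientific block of that table opens: "This deals with the assessment of treatment safety, dose, response, effect, and variance of the effect". The text below the table repeats the commitment: "Scientific uncertainties will include safety, dose, and variance of effect".

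Section 2.8 covers collection: "Questions about adverse events will be sent out prior to each exercise testing", with a pointer to supplement S7. It mentions no other occasion for these questions.

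The schedule comes from sections 2.1, 2.5 and 2.7. There are two six-week exercise periods, MICT first and then HIIT, with an eight-week washout between them and a test visit before and after each period. Every visit includes an incremental cycling test to exhaustion, with venous and capillary blood taken before and after it. The child then wears an accelerometer for seven days.

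**The concern.** Two gaps bear on the same question.

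First, Table 1 is where the article fixes its decision rule, and the Discussion presents these criteria as the basis for judging feasibility before any full-scale study. An uncertainty that is named for this analysis but has no row has no predefined level at which it counts as feasible, adjustable or unfeasible. An event that does not make a child stop, miss a procedure or rate the exercise unacceptable need not register anywhere in the table.

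Second, questions asked only ahead of each test cannot ask about the last test.

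What is at stake is the evidence handed on to the planned pilot. The study introduces repeated exhaustive testing and high-intensity intervals in children with cerebral palsy. It could meet all its criteria with no direct safety input and with an incomplete structured record of events around testing.

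**Working it through.** The plan contains no safety figure to reproduce. The check is a row count and a timeline.

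**Table 1 rows.**

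| Block | Rows | Safety rows |
|---|---|---|
| Process | 4 (recruitment, retention, data collection, outcome measures) | 0 |
| Scientific | 4 (outcome measures, acceptability, usability, barriers/facilitators) | 0 |
| Management | 2 (delivering sessions, delivering equipment) | 0 |
| Resources | 3 (intervention, testing, logistics) | 0 |
| Total | 4 + 4 + 2 + 3 = 13 | 0 |

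The four Scientific rows rest on these outcomes or criteria: "Outcomes provide interpretable data with acceptable variance"; "Perceived acceptability of the eHealth tablet app and home-based exercise"; "Technical support needed"; "Perceived barriers and facilitators when exercising and using eHealth tablet app". None is about adverse events. The text under the table also assigns acceptability, usability and barriers/facilitators to Process. On that assignment the Scientific block keeps only its variance row.

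**Timeline per child.** Tests = 2 periods × 2 = 4, with one set of questions ahead of each.

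| Adverse-event questions | Exposure since the previous set |
|---|---|
| Before test 1 | None (baseline) |
| Before test 2 | Test 1 and MICT |
| Before test 3 | Test 2 and washout |
| Before test 4 | Test 3 and HIIT |
| None stated | Test 4 |

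Tests followed by a later set: 3 of 4. Not followed: 1 of 4 = 25%. With the 20 children anticipated in section 2.3 and full attendance, that is 20 × 1 = 20 of 20 × 4 = 80 tests.

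**Sensitivity to the number of periods.** The Discussion mentions a fourth exercise period, whereas the Abstract and section 2.1 give two. If each child had four periods there would be 8 tests, and the eighth would be the uncovered one. The gap does not depend on which reading is right.

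**What a safety row could show at this size (context only).** If no child has an event, the one-sided 95% upper bound on the proportion affected is 1 − 0.05^(1/n):
- n = 20: 13.9%
- n = 10 (one group): 25.9%

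The chance of seeing at least one affected child is 1 − (1 − p)^n. The documents give no event rate, so p is an assumption:

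| Assumed p | n = 10 | n = 20 |
|---|---|---|
| 5% | 40.1% | 64.2% |
| 10% | 65.1% | 87.8% |
| 20% | 89.3% | 98.8% |

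A safety row would thus be a coarse screen, but not an empty one.

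**The case against.** The best defence is that safety information reaches the study by several other routes. Pain and exertion are scored after every session, heart rate and workload are recorded continuously, and the trainer writes field notes (section 2.8). Families can message the researchers (section 2.6). The child and caregiver are interviewed after each period, and those interviews are meant to take in the testing before and after it. The final test is a lab visit, so staff would see an acute event, and the accelerometer worn afterwards makes some later contact likely. The team also reviews findings after each period (section 2.9.4), and a pilot precedes any larger study. Finally, S7 is not shown, and a condensed article may leave reporting detail to it.

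Much of this stands, and it rules out three stronger readings that a reader might infer:

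- *That any number of events would leave every criterion at feasible.* Not supported. A child who stops because of an event lowers retention and completed sessions, and may lower data-collection completion, acceptability or barriers/facilitators.
- *That events are undercounted by design.* Not supported. The lack of a form after the last test does not show that events are missed, because the informal routes may catch them.
- *That the form before the first test is wasted.* Not supported. It gives a baseline against which later complaints can be judged.

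The defence does not remove the core. None of these routes is described as adverse-event collection or tied to a criterion. The figure giving interview times is not visible, so whether the last interview follows the last test cannot be confirmed. Part of the training uses pre-recorded video at times the child chooses, with no live supervision described. Whatever S7 contains, it does not add a row to Table 1.

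**Conclusion.** The point holds in two parts, and the protocol should be changed on both.

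- **Criterion.** Safety is named twice as an uncertainty for this analysis, and 0 of 13 rows address it, so events count towards progression only indirectly. Confidence is high, because the whole table can be read.
- **Timing.** On the stated schedule the final exhaustive test, with its blood sampling, is followed by no structured adverse-event form: 1 of 4 tests per child, up to 20 of 80. Confidence is medium. This assumes that S7 adds no closing contact; the 20 of 80 also assumes two periods per child, 20 children and full attendance.

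**What to change.** 1. Send the existing S7 questions once more after the final test, for example when the accelerometer is returned. That makes five sets instead of four, and every test is then followed by one. If S7 already provides for this, section 2.8 need only say so.
2. Add a Safety row to the Scientific block of Table 1. It could report the number of children with at least one related event and any serious event, by group (CP-A, TD) and by modality (MICT, HIIT). The investigators should set the three levels before data are reviewed, and state how the row enters the overall assessment.

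An adverse-event item in the app's post-session entry, or a form after every test, would shorten the interval before events are asked about. These are optional.

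The cost is one extra short form per family and one extra table row. The sample size, schedule and intervention do not change.

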### Data analysis and statistics

2.9

A convergent mixed methods approach will be used to assess the feasibility of the exercise intervention, the eHealth solution ability to deliver the exercise interventions and the different procedures in the effectiveness testing from multiple perspectives, integrating both quantitative and qualitative data. In this design, quantitative and qualitative data will be analysed separately and then integrated during interpretation (30).

#### Feasibility analysis

2.9.1

To structure the feasibility analysis process, scientific, management, and resource (33) uncertainties will be assessed (Table 1). The analysis will have an intent-to-treat (ITT) approach where above 66% of successful cases will be considered feasible, adjustable if successful cases fall between 20% and 65%, and unfeasible if the successful case rate is below 20%, both for individual outcomes and for an overall analysis. Wide thresholds were chosen to allow for iterative refinement of the intervention based on participatory feedback during study. When items are considered adjustable, the data collected from the android tablet computer, field notes, and interviews will be used to further develop the HOME-EX protocol.

**Table 1 T1:** Description of predefined progression criteria.

Items	Outcomes	Predefined progression criteria
***Process:*** This assesses the feasibility of the processes that are key to the success of the main study. Evaluation of study design (e.g., reducing uncertainty around recruitment, data collection, retention, outcomes, and analysis)		
Recruitment	Recruitment rate	>66% of invited participants accepted to participate in the study
		65%–20% of invited participants agreed to participate in the study
		<19% of invited participants agreed to participate in the study
Retention	Retention rate	>66% completed all exercise periods
		65–20% completed all exercise periods
		<19% completed all exercise periods
Data collection	Completion rate and perceived usefulness	>66% completed all procedures and are perceived as useful/acceptable
		65%–20% completed all procedures and perceived them as useful/acceptable
		<19% completed all procedures and perceived them as useful/acceptable
Outcome measures	Variance and distribution of collected data	Outcomes provide interpretable data with acceptable variance
		Outcomes partially interpretable, large variance
		Outcomes are not interpretable, excessive variance
***Scientific:*** This deals with the assessment of treatment safety, dose, response, effect, and variance of the effect (study design)		
Outcome measures	Variance and distribution of collected data	Outcomes provide interpretable data with acceptable variance
		Outcomes partially interpretable, large variance
		Outcomes not interpretable, excessive variance
Acceptability	Perceived acceptability of the eHealth tablet app and home-based exercise	>66% report app/exercise acceptable
		65%–20% report app/exercise acceptable
		<19% report app/exercise acceptable
Usability/technical demands	Technical support needed	Only initial introduction needed
		Required equal time for support as for tablet app use
		Unable to use eHealth app due to technical demands
Barriers/facilitators	Perceived barriers and facilitators when exercising and using eHealth tablet app	Perceived more facilitators than barriers
		Equal numbers of facilitators as barriers
		Perceived more barriers than facilitators
***Management:*** This covers potential human and data management problems		
Capacity to deliver exercise sessions	Trainers' capacity to deliver exercise intervention	>66% completed exercise sessions
		65%–20% completed exercise sessions
		<19% completed exercise sessions
Capacity to deliver exercise equipment	Logistics in delivering cycle ergometers to children's homes	>66% successful deliveries
		65%–20% successful deliveries
		<19% successful deliveries
***Recourses:*** This pertains to assessing time and resource problems that can occur during the main study		
Resources to deliver	Exercise intervention	Trainer reports delivery of exercise sessions as feasible with given resources
		Trainer reports delivery possible but challenging
		Provider reports delivery not feasible
Resources to deliver	Effectiveness testing	The coordination of all tests is feasible within resources
		The coordination of all tests is possible but challenging
		Provider reports delivery not feasible
Resources to deliver	Logistics to deliver cycle ergometers to children's homes	The coordination of all tests is feasible within resources
		The coordination of all tests is possible but challenging
		Provider reports delivery not feasible

Process uncertainties will include as recruitment rate, retention rate, acceptability, usability, barriers/facilitators, and adherence. Scientific uncertainties will include safety, dose, and variance of effect, all aspects related to the study design planned for a future efficacy study, Management uncertainties will address data collection processes, while resource-related uncertainties will assess the time and resource problems involved in running the study (33) (see Table 1 on progress criteria).

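### The progression cut-offs differ between section 2.9.1 and Table 1 and leave gaps, the ergometer-logistics row carries another row's criterion, and the usability tiers are incomplete

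*Protocol article*

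**What the plan says.** Section 2.9.1 (Feasibility analysis) sets three bands. The top one is "above 66% of successful cases will be considered feasible"; the other two are "adjustable if successful cases fall between 20% and 65%, and unfeasible if the successful case rate is below 20" per cent. The rule applies "both for individual outcomes and for an overall analysis".

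Table 1 restates the bands row by row. For recruitment they are ">66% of invited participants accepted to participate in the study", "65%–20% of invited participants agreed to participate in the study" and "<19% of invited participants agreed to participate in the study". The same three figures recur for retention, data collection, acceptability, sessions delivered and equipment deliveries, so six rows carry percentages.

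Two rows without percentages also matter here:

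- **Usability/technical demands.** The top tier is that an introduction at the start is enough. The middle tier is "Required equal time for support as for tablet app use". The bottom tier is that the app cannot be used.
- **Resources, logistics of delivering cycle ergometers.** The top tier reads "The coordination of all tests is feasible within resources". The first two tiers are identical to those of the row above, which concerns effectiveness testing.

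**The concern.** The study does not assess effectiveness, so these criteria are its main decision output. They determine whether an element goes forward, is adjusted or is judged unfeasible, and they inform whether a pilot study follows. Criteria fixed in advance should give every possible result exactly one category. Here the text and the table disagree on the lower cut-off, both leave a gap at the upper one, one row does not measure its named outcome, and one ordinal scale has a hole in its middle. Under section 2.9.4 (Integration of data) the team reviews findings after each exercise period and may change later periods. A result in a gap would then be classified with the data already in view.

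**Working it through.** **Inputs**

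- Text rule (section 2.9.1): feasible >66%; adjustable 20% to 65%; unfeasible <20%.
- Table 1 rule (six percentage rows): feasible >66%; adjustable 20% to 65%; unfeasible <19%.
- Children: 20 anticipated, ten per group (section 2.3).
- Sessions: 3 per week × 6 weeks × 2 periods = 36 per child (section 2.5), and 36 × 20 = 720 if all children start both periods and sessions are pooled. The article does not say whether they are pooled.
- Number invited: not given. Totals of 20 to 100 are taken as an assumed range.

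**Bands side by side**

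| Result | Text | Table 1 |
|---|---|---|
| below 19% | unfeasible | unfeasible |
| 19% to <20% | unfeasible | none |
| 20% to 65% | adjustable | adjustable |
| >65% to 66% inclusive | none | none |
| above 66% | feasible | feasible |

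The two rules differ only in the second line. They never assign two different categories to one result.

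**Which counts k out of n fall in a gap** (k/n classified with exact fractions)

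- n = 20: none. 3/20 = 15%, 4/20 = 20%, 13/20 = 65%, 14/20 = 70%. At n = 10 there are also none.
- n = 21: 4/21 = 19.05%, unclassified in the table and unfeasible in the text.
- n = 23: 15/23 = 65.22%, unclassified in both.
- n = 36 (one child's sessions): 7/36 = 19.44%, unclassified in the table and unfeasible in the text.
- n = 720 (pooled sessions): 137 to 143 (19.03% to 19.86%) are unclassified in the table only; 469 to 475 (65.14% to 65.97%) are unclassified in both. That is 14 of 721 possible counts, or 1.9%.
- Recruitment, n = 20 to 100 invited: 60 of the 81 totals contain at least one count unclassified in the table, but this is 90 of 4,941 possible results, or 1.8%. With exactly 20 acceptances no total in that range is affected; the first affected totals are 101 to 105 invited (20/101 = 19.80% to 20/105 = 19.05%).

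**Does rounding to whole per cent close the gaps?** No. A rounded 19% is not below 19, and a rounded 66% is not above 66. At n = 720, counts 134 to 140 and 472 to 478 round to those two values.

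**Rows without percentages**

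- *Ergometer logistics.* The outcome is delivery to homes; the first two tiers ask about coordinating tests, which take place in the exercise lab (section 2.4). Only the third tier, a provider's report that delivery is not feasible, fits the outcome.
- *Usability.* Support beyond the introduction but short of the time spent in the app belongs to no tier. Nor does support exceeding that time while the app can still be used.

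**The case against.** The strongest reply is that these are drafting slips with little practical reach. Much of it stands. At the planned 20 children no per-child criterion is touched. From 19% to just under 20% the text supplies a verdict where the table is silent. Each percentage gap is about one point wide and lies between adjacent categories. The ergometer row's outcome label is clear, and delivery has its own correct percentage row under Management. Usability is explored mainly through qualitative data (section 2.9.3). An adjustable rating leads to refinement, and a pilot with probably stricter thresholds is planned.

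Some of it does not stand. Twenty children is an anticipated number, with recruitment to saturation, and one extra child already opens a gap. The Management row counts successful deliveries; it does not assess the resources they need, which the Discussion treats as essential for a home-based intervention. The limitation stated there about wide thresholds concerns their width and does not cover gaps or a mismatch.

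Two stronger readings are tempting. A reader might infer from the 60 of 81 invitation totals that most recruitment results are at risk; that figure only asks whether any count, however unlikely, hits a gap, and fewer than 2% do. A reader might also infer that the overall verdict could be feasible with several rows failed, by taking it as the share of rows met. The article speaks of successful cases, not rows, and its Discussion describes a summary assessment once all outcomes are collected, so that reading is conjecture. A rule tying the overall verdict to the worst key item would be a design preference. If it named adherence or safety, it would also rest on items without a named row in Table 1.

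**Conclusion.** The point holds and should be fixed, though it does not threaten the study. Four defects are plain on the page: a lower cut-off of 20% in the text against 19% in six table rows, an unclassified band above 65% up to and including 66% in both places, an ergometer-logistics row that does not assess its own outcome, and usability tiers with an uncovered middle. The percentage gaps affect about 2% of possible session or invitation counts and no head-count at n = 20. The session figure for n = 720 assumes pooling and full participation; the recruitment figure assumes 20 to 100 invited. The usability gap cannot be sized from the article, but it covers ordinary follow-up support and may therefore be reached more readily than the one-point percentage gaps.

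**What to change.** 1. Use one rule in section 2.9.1 and in all six percentage rows: feasible >66%; adjustable 20% to 66% inclusive; unfeasible <20%. This keeps the upper cut-off on which text and table already agree. Every result then has exactly one category. At n = 20 nothing changes (0–3 unfeasible, 4–13 adjustable, 14–20 feasible); at 720 pooled sessions the bands become 0–143, 144–475 and 476–720.
2. In the Resources row on ergometer logistics, replace the test-coordination wording with tiers on the resources for delivering ergometers: feasible within the resources, possible but challenging, not feasible.
3. In the usability row, let the middle tier cover any support beyond the initial introduction for as long as the app can still be used. This needs no new numerical boundary.

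The cost is one sentence in section 2.9.1 and edits to Table 1. There is no effect on sample size or data collection. The edits should be dated and made before results are reviewed.

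### The percentage progression bands leave gaps and differ between section 2.9.1 and Table 1, so a few attainable borderline results have no clear classification (minor)

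*Protocol article*

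**What the plan says.** Section 2.9.1 (Feasibility analysis) states the rule in one sentence. At the top, "above 66% of successful cases will be considered feasible". Below that, a result is "adjustable if successful cases fall between 20% and 65%, and unfeasible if the successful case rate is below 20" per cent. The sentence applies the rule "both for individual outcomes and for an overall analysis".

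Table 1 then gives the criteria item by item. For recruitment the three lines are ">66% of invited participants accepted to participate in the study", "65%–20% of invited participants agreed to participate in the study" and "<19% of invited participants agreed to participate in the study". Retention ends with "<19% completed all exercise periods", and the trainer-capacity item ends with "<19% completed exercise sessions". The same three limits (>66, 65–20, <19) appear in all six percentage items: recruitment, retention, data collection, acceptability, session delivery and equipment delivery. The article gives no rounding rule.

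**The concern.** A three-band progression rule should place every possible result in exactly one band, and should read the same wherever it is stated. This one does neither. The top band starts above 66% while the middle band stops at 65%. The bottom band starts below 20% in the text but below 19% in the table.

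The band decides what happens next. Under section 2.9.1, an adjustable item is one for which tablet data, field notes and interviews are used to develop the protocol further. Section 2.9.4 has the team review findings after each exercise period, so the rule may be consulted more than once. A result that falls in a gap would have to be classified after it is known, which is what predefined criteria are meant to prevent.

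**Working it through.** **Bands side by side**

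| Rate p | Section 2.9.1 | Table 1 (six percentage items) |
|---|---|---|
| p > 66% | feasible | feasible |
| 65% < p ≤ 66% | no band | no band |
| 20% ≤ p ≤ 65% | adjustable | adjustable |
| 19% ≤ p < 20% | unfeasible | no band |
| p < 19% | unfeasible | unfeasible |

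The next question is whether real results can fall in the second and fourth rows.

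**Items counted on children.** Section 2.3 anticipates 20 children, 10 per group. Rates then move in steps of 5 or 10 points. Around the limits, 13/20 = 65% (adjustable), 14/20 = 70% (feasible), 4/20 = 20% (adjustable) and 3/20 = 15% (unfeasible). Nothing falls in a gap, and the same is true for every denominator of 20 or less. Section 2.3 also says that recruitment continues until saturation. If more than 20 children enrol, gap results become possible: 4/21 = 19.05%, 15/23 = 65.22%, 17/26 = 65.38%, 19/29 = 65.52%.

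**Sessions.** Inputs are three sessions a week (section 2.5, same weekly plan for both modalities) and two six-week periods (section 2.1). Per child: 3 × 6 × 2 = 36. For 20 children: 36 × 20 = 720. Using all 720 as the denominator is an assumption, because the article does not define one.

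- Upper gap: 0.65 × 720 = 468 and 0.66 × 720 = 475.2, so totals of 469–475 (65.14%–65.97%) have no band in text or table.
- Lower gap: 0.19 × 720 = 136.8 and 0.20 × 720 = 144, so totals of 137–143 (19.03%–19.86%) are unfeasible in the text and in no band in the table.

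Other plausible denominators give the same picture:

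| Denominator | Example | Upper gap | Lower gap |
|---|---|---|---|
| 36 | one child | none | 7 |
| 180 | one group, one period | 118 | 35 |
| 360 | one group, or one period, or only the three live-supervised weeks per period (3 × 3 × 2 × 20) | 235–237 | 69–71 |
| 720 | 20 children, two periods | 469–475 | 137–143 |
| 1440 | four periods per child, if the fourth period in the Discussion were read that way | 937–950 | 274–287 |

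On 720 sessions there are 721 possible totals. Table 1 leaves 7 + 7 = 14 without a band (about 2%), and the text leaves 7.

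**Recruitment.** The number invited is not given, so these figures are illustrations. If 20 accept, 101–105 invited gives 19.80%–19.05%, in the lower gap. If 10 accept, 51–52 invited does the same. Exactly 20 acceptances cannot fall in the upper gap, because 20/0.66 = 30.30 and 20/0.65 = 30.77 have no whole number between them. Neighbouring counts can: 17/26, 19/29 and 21/32 (65.62%).

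**Rounding.** Rounding to whole percentages does not close the gaps. A rounded 66% is not above 66 and not within 20–65. A rounded 19% is unfeasible in the text and is not below 19 in the table.

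**The case against.** The strongest reply is that very little turns on this. Each gap is about one percentage point wide. Retention, data collection and acceptability are naturally counted on children, as is equipment delivery if there is one delivery per child, and at the planned size none of these can land in a gap. In the lower gap the text does give a verdict, and it is the one that a repaired table would give. The upper gap separates feasible from adjustable, and the information that an adjustable verdict calls on is collected from everyone in any case. The team reviews findings after each period, and the Discussion plans a summary assessment over all outcomes. The article also says that the thresholds are deliberately wide and that a later pilot will probably use stricter ones. All of this stands, and it limits the importance of the point. It does not make the two statements agree, and it gives the upper gap no verdict.

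Three stronger readings are tempting and are not supported:

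- A reader might infer that some results receive two opposing verdicts. None does. The disagreement is always between a verdict in the text and silence in the table.
- A reader might infer that these bands are the study's only quantitative rule. Table 1 also compares numbers of barriers with facilitators, and support time with time using the app.
- A reader might take the 720 sessions or the 101–105 invitations as the protocol's own denominators. They are assumptions. The session item concerns the trainer's capacity and might count live sessions only. The session gaps persist under each total shown, but the exact counts change.

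**Conclusion.** The inconsistency is real and minor. It can be read directly from the current text, and because the under-19% limit recurs in all six percentage items it is not a slip in a single row. Rates above 65% and up to 66% have no verdict anywhere; rates from 19% to under 20% have one only in section 2.9.1. At the planned 10 or 20 children the reach is confined to session-level rates and to recruitment. It extends to child-level items only if enrolment goes beyond 20. The existence of the gaps rests on no assumption; the worked counts rest on the assumed session totals and invitation numbers.

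**What to change.** Use one contiguous set of bands in section 2.9.1 and in every percentage item of Table 1: feasible if above 66%, adjustable if at least 20% and at most 66%, unfeasible if below 20%, applied to unrounded proportions. This leaves unchanged the upper cut-off on which text and table already agree, and classifies every result exactly once. Lowering the top band to include 66% would also close the gap, but it would move a criterion that is currently stated consistently, so it is not preferred.

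The cost is one sentence in section 2.9.1 and the middle and lower lines of six items in Table 1 (6 × 2 = 12 lines). Design, sample and data collection are unaffected. Section 2.10 reports recruitment in progress, so the wording should be settled before any feasibility rates are reviewed.
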